# Can dexamethasone improve postoperative sleep and postoperative delirium in elderly patients undergoing robot-assisted laparoscopic radical prostatectomy? Protocol for a prospective, randomized, double-blind, controlled study

**DOI:** 10.1186/s13063-023-07521-8

**Published:** 2023-08-08

**Keywords:** Dexamethasone, Robot-assisted radical prostatectomy, Elderly patient, Enhanced recovery after surgery, Postoperative delirium, Perioperative sleep disorders

## Abstract

**Background:**

Perioperative sleep disorders (PSD) are an independent risk factor for postoperative delirium (POD), which is a common complication after surgery. Elderly patients who undergo robot-assisted radical prostatectomy (RARP) often experience perioperative sleep disorders (PSD). Dexamethasone, a medication that works by inhibiting the hypothalamic-pituitary-suprarenal cortical axis, can reduce the negative effects of surgical stress. The objective of this study was to determine whether intravenous administration of dexamethasone at the time of anesthesia induction could improve postoperative sleep quality in elderly patients, thereby indirectly reducing the risk of postoperative cognitive impairment and accelerating postoperative rehabilitation.

**Methods/design:**

This study is a randomized, double-blind, placebo-controlled trial that was conducted at a single center. A sample size of 116 patients was determined through calculation, and these patients were randomly assigned to either the dexamethasone group (group D, *n* = 58) or the blank control group (group C, *n* = 58). On the day of surgery, the anesthesia nurse prepared either diluted dexamethasone or saline in advance, according to the patient's assigned group. The blinded anesthesiologist administered the medication during induction, and a dedicated person followed up with the patient for three consecutive postoperative days. All other aspects of care were managed equally between the two groups. The primary outcome measure was sleep quality, while secondary outcome measures included postoperative sleep time, postoperative delirium (POD), pain scores, and other complications. Relevant test measures were recorded for analysis.

**Discussion:**

This study aims to investigate the impact of intravenous dexamethasone on sleep quality and duration of patients undergoing robot-assisted radical prostatectomy (RARP). If the findings of this study protocol are affirmative, it could enhance the sleep quality of elderly patients after surgery, thereby minimizing the risk of postoperative delirium (POD), and providing substantial evidence for the perioperative enhanced recovery management of elderly patients.

**Trial registration:**

Chinese clinical trial registry: ChiCTR2200063488, Registered on 5 October 2022.

**Supplementary Information:**

The online version contains supplementary material available at 10.1186/s13063-023-07521-8.

## Background

Prostate cancer is the second most commonly diagnosed cancer and the sixth leading cause of cancer-related death in males. It is the most prevalent male urinary tumor in economically developed countries, and its incidence is higher in elderly patients who often have coexisting medical conditions [1]. Enhanced recovery after surgery (ERAS) interventions are widely adopted in general surgery, hepatobiliary surgery, and gynecology. However, there is limited research on the effectiveness of ERAS interventions in elderly patients [2, 3]. Postoperative sleep disturbance (PSD) is a common complication following surgery. In China, sleep disorders affect around 46.0% of elderly individuals, with 40.0% prevalence in elderly males. This is a frequent symptom among the elderly population [4]. Chronic sleep deprivation (SD) can impair the recovery and treatment of elderly patients with underlying medical conditions, as well as increase the risk of cardiovascular and cerebrovascular diseases, such as hypertension and cerebral infarction. It can also lead to postoperative delirium (POD), which is a significant risk factor for poor postoperative rehabilitation in the elderly [5]. Patients frequently experience severe sleep disorders during the perioperative period, which can be attributed to factors such as surgical environment, pain, and anxiety [6]. Therefore, it is crucial to focus on preventing and treating sleep disorders in the elderly during the perioperative period. Research has indicated that age is a significant risk factor for postoperative delirium (POD) [7, 8]. Moreover, various degrees of sleep deprivation, disruption, and abnormal sleep patterns before surgery can increase the incidence of POD [9].

Abnormal sleep patterns have been identified as an independent risk factor for postoperative delirium [10]. Improving sleep can help reduce the incidence of postoperative delirium.

Research has demonstrated that dexamethasone can diminish cortisol secretion via negative feedback inhibition of the hypothalamus-pituitary-suprarenal gland cortical axis, which could potentially ameliorate a range of negative effects caused by surgical stress and improve sleep quality [6, 11]. Other studies have indicated that preoperative administration of dexamethasone may lower the incidence of POD [12]. Additionally, some studies have reported that elevated serum cortisol levels in the early postoperative period are linked to a heightened risk of cognitive impairment [7, 13]. Furthermore, by diminishing cortisol secretion via negative feedback inhibition of the hypothalamus-pituitary-suprarenal gland cortical axis, dexamethasone can mitigate a variety of negative effects caused by surgical stress, subsequently improving postoperative insomnia and other symptoms [14, 15]. Our preliminary experiment revealed that dexamethasone has the potential to decrease inflammation, alleviate pain, and improve postoperative sleep. Furthermore, our findings indicate that there are no established guidelines for the clinical use of dexamethasone, and most anesthesiologists administer it based on their personal preferences. Therefore, we aim to investigate whether administering dexamethasone during anesthesia induction can ameliorate postoperative delirium, improve sleep quality among elderly patients after RARP, and ultimately facilitate enhanced recovery after surgery (ERAS).

## Methods

### Trial design

This trial is a single-center, randomized, double-blind, and placebo-controlled study. The study is structured as a parallel grouping with an allocation ratio of 1:1, embracing the framework of a superiority trial.

Changhai Hospital, located in Shanghai, China, is a comprehensive medical institution that integrates clinical practice, teaching, and research. Its Urology Department is among the top-ranking centers in China and is equipped with the most state-of-the-art Da Vinci surgical robot worldwide. Each year, a large number of patients flock to the hospital, drawn by its reputation. Patients who meet the specified criteria will be recruited through recruitment advertisements, with the deadline for recruitment projected to be June 31, 2024. Competent anesthesiologists in specialized preoperative evaluation clinics and wards will be responsible for selecting patients scheduled to undergo robot-assisted laparoscopic radical prostatectomy. We anticipate achieving a recruitment rate of 150%, with an estimated enrollment of 20 patients per month. The expected duration for recruitment is one year. The details of the research plan will not be disclosed to any previously involved medical personnel, and the exclusive responsibility for patient recruitment will be entrusted to specialized anesthesiologists. Patients who fail to meet the inclusion criteria will be excluded. Furthermore, patients who enroll in the trial have the right to discontinue participation and withdraw at any time. If a patient chooses to participate in the trial, they must provide a complete medical history and answer the investigator's questions truthfully. The patient's personal data will be safely stored and protected by the investigator. The trial is expected to be completed by December 2024. Patients will receive detailed information about the study's purpose, risks, and benefits prior to surgery, and must provide written informed consent before initiation of the study. The investigators will complete a case report form (CRF) that includes age (in years), height, weight, and the American Society of Anesthesiologists (ASA) classification. This reported protocol was in accordance with the Standard Protocol Items: Recommendations for Intervention Trials (SPIRIT) guidelines [16].

### Registration and ethics approval

On July 27th, 2022, the ethics committee of Shanghai Changhai Hospital granted approval for the trial under the number CHEC2022-132. Furthermore, the trial was registered with the Chinese Clinical Trial Registry under the registration number ChiCTR2200063488.

### Inclusion criteria

A)Participants underwent elective robotic-assisted laparoscopic radical prostatectomy;B)Participants were 65 years of age or older;C)Participants with American Society of Anesthesiologists (ASA) physical status classifications I to III were included;D)Patients who had a Pittsburgh Sleep Quality Index (PSQI) score of ≥ 7 for nearly one month preoperatively were evaluated; A PSQI score of ≤ 6 indicated good sleep, while a score of ≥ 7 indicated the presence of a sleep disorder and eligibility for trial enrollment. (The PSQI total score ranges from 0 to 21, with higher scores indicating worse sleep quality.)E)Participants who woke up before 5 PM were included; andF)Participants had clear consciousness and normal communication ability.

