### Randomization and blinding

In order to mitigate selection bias, randomization and allocation concealment were conducted by a medical statistician prior to the commencement of the trial. The patients were randomly assigned to two groups in a 1:1 ratio using SPSS 26.0: the dexamethasone group (group D) and the control group (group C). Post-randomization information was sealed in 116 brown paper envelopes and stored in sequence in cabinets. On the day of surgery, the envelopes were opened in sequence based on group assignment and read by an anesthesia nurse on the research team. Dexamethasone or saline was prepared based on the randomization. An anesthesiologist who was blinded to the group assignments conducted the trial. A specialized anesthesiologist performed the outcome assessment, while another anesthesiologist carried out the data analysis. Both of them were unaware of the group allocations. Details regarding patient recruitment advertisement can be obtained from the corresponding author. [name], a valued member of the research team, assumes the pivotal role of patient recruitment. [name] diligently arranges a preoperative visit with the patient the day prior to their scheduled surgery. During this essential preoperative encounter, her primary objective is to ensure that the patients possess a thorough understanding of the study and the clinical significance of their participation, while also obtaining their signed informed consent for the trial.

We will request consent for review of participants' medical records, and for the collection of blood samples to assess Hemoglobin, albumin, serum sodium, testosterone, cortisol, IL-6, TNF, NSE, and Sβ-100 were recorded before surgery, 1 day and 2 day after surgery. The patient's blood specimens will be collected by dedicated laboratory personnel. After proper processing, these samples will be stored in an ultra-low temperature freezer at − 80℃ for subsequent molecular biology experiments and surveillance.

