### Experimental process

Before surgery, all recruited patients scheduled for elective robot-assisted radical prostatectomy were selected based on the inclusion criteria mentioned above, assessed using the PSQI scale, and screened for eligibility based on the exclusion criteria mentioned above. Standardized perioperative management and postoperative care process were uniformly implemented for the enrolled patients, which included preoperative preparation according to the standard surgical routine. The general flow chart and trial schedule are displayed in Fig. 1 and Table 1, respectively.

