**Enrollment**							
Eligibility screening		**X**					
Informed consent		**X**					
Random allocation		**X**					

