#### Secondary outcome

Secondary outcomes included postoperative sleep time, incidence of postoperative delirium (POD), VAS pain score, analgesic use and dosage, blood test indexes (hemoglobin, albumin, blood sodium, testosterone, cortisol, IL-6, TNF-α, NSE, and S β-100), and perioperative-related indicators (operation time, anesthesia time, intraoperative blood loss and fluid volume, sufentanil and remifentanil dosage, vasoactive drug type and dosage, and awakening time from the end of the operation to extubation time). The postoperative sleep time was assessed based on the patient's self-reported time of falling asleep to waking up. The CAM method was used for POD diagnosis, requiring positive scores for feature 1 plus 2 and feature 3 or 4 to be considered positive for CAM (Table 2). The use of analgesics and their dosage were recorded.

**Table 2 Tab2:** Confusion assessment method (CAM)

Characteristic	Manifestations
Acute onset and fluctuating course	Whether there is evidence of an acute change in mental status compared with the patient’s basal level
	Whether the patient's (abnormal) behavior fluctuates over the course of 1 day (symptoms are sometimes absent or mild and sometimes severe)
Inattention	Whether patients have difficulty concentrating, such as attention is easily distracted or cannot keep up with the topic being talked about
Disorganized thinking	Whether the patient’s thinking is disorganized or incoherent, such as when the topic of conversation is scattered or irrelevant, thinking is unclear or illogical, or suddenly changes from one topic to another without warning
Altered level of consciousness	Whether the patient’s current level of consciousness is abnormal, such as hypervigilance (excessive sensitivity to environmental stimuli, startle easily), somnolence (drowsiness, easy to wake up), or coma (difficult to wake up)

Scoring criteria: delirium was diagnosed with characteristic 1 plus 2 and characteristic 3 or 4 positive = CAM positive

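### Inclusion criterion E (awake before 5 PM) is undefined and, on its natural reading, can be judged only after allocation and dosing

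*Protocol article*

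**What the plan says.** The protocol article, Inclusion criteria, item E: "Participants who woke up before 5 PM were included". Neither the event nor the day is defined. Under Trial design the consequence of failing is general: "Patients who fail to meet the inclusion criteria will be excluded".

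Eligibility is placed before the operation. Experimental process says: "Before surgery, all recruited patients scheduled for elective robot-assisted radical prostatectomy were selected based on the inclusion criteria mentioned above". Table 1 marks eligibility screening, consent and "Random allocation" together in its preoperative part. Randomization and blinding adds: "On the day of surgery, the envelopes were opened in sequence based on group assignment and read by an anesthesia nurse". The same section says "Post-randomization information was sealed in 116 brown paper envelopes", which equals the target sample size. Table 1 and the text below it put the study drug at induction (T2).

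Among the secondary outcomes are operation time, anesthesia time and "awakening time from the end of the operation to extubation time". The Rejection criteria remove patients for withdrawal, for incomplete sleep or cognitive assessment, and for a second operation. Late awakening is not among them.

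**The concern.** An eligibility rule should be decidable before allocation. If this one refers to emergence from anaesthesia, it is decided by what happens after allocation and treatment. Excluding patients who fail it would then make the analysed set depend on post-treatment events, and the comparison would no longer be of the groups as randomised.

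Those removed would tend to be patients with late or long operations and slow recovery. The Discussion names surgical duration among the factors that could affect postoperative sleep quality, which is the primary outcome. So the patients lost could plausibly differ on that outcome. Because the rule sits among the inclusion criteria and not the Rejection criteria, the loss might also be reported as ineligibility when it is in fact exclusion after treatment.

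**Working it through.** **1. Order of events in the article**

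1. Screening against the inclusion criteria, consent and random allocation: preoperative (Experimental process; Table 1).
2. Envelope opened and syringe prepared: day of surgery (Randomization and blinding).
3. Dexamethasone or saline given: induction, T2 (Table 1).
4. Surgery begins and ends: T3 and T4.
5. Awakening: after T4, recorded as wake time from end of surgery to extubation (Experimental process).

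If criterion E means step 5, it cannot be met or failed at step 1.

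**2. Other readings**

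- Habitual waking time would be known beforehand, but a 5 PM limit would exclude almost nobody.
- Expected or scheduled awakening by 5 PM would also be known beforehand, but the criterion contains no word such as planned or expected.

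Either reading would also need the text to be corrected.

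**3. What the clock time contains**

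Clock time of awakening = start time + operation time + time to awakening. The last two terms are listed secondary outcomes. The overlap is therefore with components of the criterion, not with the criterion itself.

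**4. Power**

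Inputs from Sample size calculating: 5.6 ± 2.0 against 6.8 ± 1.6, two-sided α = 0.05, power 0.90, 20% dropout.

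- δ = 6.8 − 5.6 = 1.2; σ = √((2.0² + 1.6²)/2) = 1.811.
- n = (1.96 + 1.28)² × 2 × 1.811² / 1.2² = 47.8, so 48 per group, as stated.
- 48 × 1.2 = 57.6, so 58 per group and 116 in total, as stated.
- Power with m per group: Φ((δ/σ) × √(m/2) − 1.96), with δ/σ = 0.6626.

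The article gives no late-awakening rate. The rates below are assumptions, applied on top of the 20% dropout.

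| Assumed loss through E | Randomised patients affected (of 116) | m per group | Power |
|---|---|---|---|
| 0% | 0 | 58 × 0.8 = 46.4 | 89.1% |
| 5% | 5.8 | 46.4 × 0.95 = 44.1 | 87.5% |
| 10% | 11.6 | 46.4 × 0.90 = 41.8 | 85.7% |
| 20% | 23.2 | 46.4 × 0.80 = 37.1 | 81.4% |

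The first row is slightly under 90% because 46.4 is below 48.

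**5. Selection, illustration only**

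Assumptions that are not in the article: no treatment effect on the Athens Insomnia Scale (AIS); 20% of patients in each arm recover slowly and score d = 1 or 2 points worse; only these patients wake late; a share p of the arm is removed. The mean excess left in an arm is d × (0.20 − p)/(1 − p).

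- Removal of 10% in both arms: difference 0.
- Control 15%, dexamethasone 5%, d = 1: 0.15/0.95 − 0.05/0.85 = 0.158 − 0.059 = 0.10.
- Control 20%, dexamethasone 5%, d = 2: 2 × 0.158 − 0 = 0.32.

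Against the planned difference of 1.2, 0.10 is 8% and 0.32 is 26%, if the pilot score is the AIS (the sample size section does not name the scale). The sign reverses if the imbalance reverses.

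**The case against.** The inclusion criteria are written in the past tense throughout. Item A, that participants had undergone the operation, would also be unknowable at screening if taken literally, yet it plainly stands for a plan. Item E may be a loose rendering of a scheduling rule, and preoperative screening may be evidence for that intention. This stands to the extent that awakening from anaesthesia cannot be called the only workable sense. It does not rescue the text, because the scheduling reading needs words that are absent.

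A reader might infer that the plan removes treated patients selectively and so biases the comparison. The article does not show this. It does not say how item E is applied or whether late wakers are followed and analysed. The Rejection criteria do not name them, and only the general sentence in Trial design points to exclusion. Any removal would apply to both arms. The anesthesiologist and the outcome assessor are blinded, and the place on the operating list does not depend on the study drug. Bias between arms would need treatment to shift awakening across 5 PM, and the article gives no such effect. Blinding does limit deliberate selection, but it does not undo conditioning on a post-treatment event.

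A reader might also infer that the awakening-time outcome is cut off. It is an interval and item E is a time of day: a slow waker early on the list passes, and a fast waker late on the list may fail. The interval is only one component of the clock time and is not cut at any fixed value.

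Finally, the article does not say what the 20% dropout covers. At an assumed 10%, the 11.6 patients would fit within the 23.2 that the allowance represents (116 × 0.20), and power would then not fall below the planned basis.

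**Conclusion.** The point holds as a defect in the eligibility rule. Item E is undefined, and on its natural reading it conflicts with preoperative screening and allocation. Combined with the general exclusion sentence, it would act as an exclusion after randomisation that the Rejection criteria do not list, driven partly by operation time and time to awakening.

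The main reason to change it is to protect the randomised comparison. The documents support a risk of bias, of unknown size and direction, and no more than that; equal removal in the two arms gives no spurious difference in the illustration. Loss of power is a minor reason: from 89.1% to 87.5% or 85.7% at assumed late-awakening rates of 5% or 10%, and only if those losses come on top of the 20% dropout. With exactly as many envelopes as the target sample size, the article describes no spare allocations to replace patients removed after opening. The change should be made. Confidence is moderate, because the meaning of the criterion and the rate of late awakening are both unknown.

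**What to change.** Replace item E with a condition that can be judged before the envelope is opened, for example the scheduled operating slot, or delete it. State that every randomised patient stays in follow-up and in the primary analysis whatever the actual time of awakening. If late awakening is thought to disturb the first-night assessment, record the clock time and add a sensitivity analysis restricted to patients awake before 5 PM, labelled as conditional on a post-treatment event. If patients have already been removed under item E, report their number and reason by arm.

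The cost is a short amendment and some added noise in the first-night AIS from the late cases that remain.

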### Exclusion criteria

A)Adrenal disease;B)Severe hypertension, neuropsychiatric disease, and significant dysfunction of the cardiac, pulmonary, hepatic, and renal systems;C)History of alcohol or substance abuse;D)History of cerebral infarction or ICH within the last 6 months;E)Long-term use of sedative or antidepressant medications; andF)Preoperative exclusion criteria based on Mini-Mental State Examination (MMSE) score.

### Rejection criteria

Patients who meet any of the following criteria will be excluded from the study:A)Patients who withdrew from the trial midway will be excluded from the study;B)Patients who could not complete self-examination of sleep quality and cognitive assessment due to uncoordinated follow-up will be excluded from the study;C)Patients who underwent secondary surgery will be excluded from the study.

